## Abstract

**Background and aim:**

Long Covid is a significant public health concern with potentially negative implications for health inequalities. We know that those who are already socially disadvantaged in society are more exposed to COVID-19, experience the worst health outcomes and are more likely to suffer economically. We also know that these groups are more likely to experience stigma and have negative healthcare experiences even before the pandemic. However, little is known about disadvantaged groups’ experiences of Long Covid, and preliminary evidence suggests they may be under-represented in those who access formal care. We will conduct a pilot study in a defined geographical area in London, United Kingdom to test the feasibility of a community-based approach of identifying Long Covid cases that have not been clinically diagnosed and have not been referred to Long Covid specialist services. We will explore the barriers to accessing recognition, care, and support, as well as experiences of stigma and perceived discrimination.

**Methods:**

This protocol and study materials were co-produced with a Community Advisory Board (CAB) made up primarily of people living with Long Covid. Working with voluntary organisations, a study leaflet will be distributed in the local community to highlight Long Covid symptoms and invite those experiencing them to participate in the study if they are not formally diagnosed. Potential participants will be assessed according to the study’s inclusion criteria and offered the opportunity to participate if they fit them. Awareness of Long Covid and associated symptoms, experiences of trying to access care, as well as stigma and discrimination will be explored through qualitative interviews with participants. Upon completion of the interviews, participants will be offered a referral to the local social prescribing team to receive support that is personalised to them potentially including, but not restricted to, liaising with their primary care provider and the regional Long Covid clinic.

## Background

Long Covid is a patient-coined term, initially defined as not recovering from SARS-CoV-2 infection after at least 4 weeks from onset [1, 2]. The World Health Organization (WHO) defines post COVID-19 condition (also known as Long Covid) as the condition that occurs in those with probable or confirmed SARS-CoV-2 infection, usually three months from onset with symptoms and that last for at least two months, not explained by an alternative diagnosis and impacts everyday functioning [3]. The Office for National Statistics (ONS) estimated that as of June 2022, two million people are currently living with Long Covid in the UK [4] and around 12% of those who tested positive for COVID-19 up to August 2021 (including those initially asymptomatic) experience symptoms consistent with Long Covid for at least 12 weeks from infection [5]. Of those living with Long Covid, 72% experience limitations of their day-to-day activities, with 21% describing their day-to-day activities as ‘limited a lot’ by Long Covid [5]. It disproportionately affects people living in more deprived areas (as measured by the English Index of Multiple Deprivation, IMD [6]), those with another health condition or disability, and those in frontline professions, such as teachers, health care professionals and people working in social care [4].

Common symptoms of Long Covid include fatigue, shortness of breath, headache, cognitive dysfunction (‘brain fog’), chest pain, muscle and joint pains, cough, disturbed sleep, and psychological symptoms, such as anxiety and depression. These symptoms often relapse and vary at different times and can be unpredictable in nature [7, 8]. Evidently, Long Covid is a significant burden and public health concern. Symptoms of Long Covid can cause difficulty sustaining employment as well as increasing the need for social support [7, 8]. In November 2020, an online survey was conducted through social media of people reporting Long Covid who were not initially hospitalised for COVID-19 during the acute phase. This survey explored the characteristics and impact of Long Covid in more than 2500 people and found that 10% of people living with Long Covid had to work reduced hours, 19% reported being unable to work at all and 38% had suffered a loss of income due to their symptoms [7]. These findings suggest that Long Covid has economic, as well as health, impacts. Therefore, the multifaceted effects of Long Covid need further exploration across different population groups.

Before the pandemic health disparities existed between different population groups. People from ethnic minority backgrounds or socially and economically disadvantaged people are likely to have poorer health outcomes when compared to people from a White British background or those living in more asset-rich areas [9, 10]. The COVID-19 pandemic has increased the visibility of these inequalities. Recent analysis shows that between January and February 2022 (when Omicron was the dominant SARS-CoV-2 variant) COVID-19 death rates were higher for ethnic minority groups compared with White British group in England [11]. During the first and second waves, prevalence rates and mortality rates for COVID-19 were highest in ethnic minorities and those living in deprived areas [12, 13]. COVID-19 is also estimated to be between three and eight times more likely to result in death for people with learning difficulties compared to other adults [14, 15].

Given these disparities in SARS-COV-2 infection and adverse health outcomes, we would expect to see high need from those in ethnic minority and more deprived communities for Long Covid care and support. However, there is some evidence that individuals from socioeconomically disadvantaged and Black, Asian and minority ethnic backgrounds may be under-represented in accessing Long Covid healthcare services [16]. Also, primary care is not provided with additional resources to address such inequalities in diagnosis and access to care [17]. To our knowledge, there is currently no evidence into how people with learning difficulties are affected by Long Covid.

Historically, some minority communities have struggled with stigma and discrimination and have had negative experiences when using healthcare services [9, 18]. This includes experiences of prejudicial attitudes and poor or inappropriate treatment [18, 19]. Long Covid, in itself, can be a stigmatising experience [20, 21]. People with Long Covid report feeling unsupported, disbelieved, and dismissed by healthcare professionals [20, 21]. Fear of repeating these experiences and further stigmatisation could be causing under-representation of socioeconomically disadvantaged groups in Long Covid primary and secondary care health services. In a survey of almost 1000 people, the authors found a prevalence of 95% and 76% of experiencing Long Covid associated stigma at least ‘sometimes’ and ‘often/always’ respectively [22]. Stigma levels were high across three domains: enacted (overt experiences of discrimination), internalised (internalising negative associations with Long Covid and accepting them as self-applicable) and anticipated (expectation of bias/poor treatment by others) stigma [22]. There is a need to explore the barriers to recognition and access to care in those with probable Long Covid. This active case finding pilot, will test the feasibility of a community-based approach of identifying probable Long Covid cases that have not been clinically diagnosed and are not receiving care, whilst exploring the reasons for this and the barriers faced when attempting to obtain a diagnosis and access care and support.

### Aims and objectives

The aim of this pilot study is to co-design, with a Community Advisory Board (CAB), and conduct an active Long Covid case-finding pilot in a specific geographical area.

#### Objectives

Find probable Long Covid cases not receiving recognition and care using a community-based approachProvide a sampling frame for in-depth qualitative interviews with people living with Long Covid not accessing Long Covid NHS servicesExamine the characteristics of people living with Long Covid identified through this pilot to inform clinical and social care/support pathways

## Methods

This pilot study was developed using a research co-production approach with people with lived experience of Long Covid. This was done as part of STIMULATE-ICP (Symptoms, Trajectory, Inequalities and Management: Understanding long COVID to Address and Transform Existing Integrated Care Pathways) study, which is a National Institute for Health and Care Research (NIHR) supported multi-centre study. It combines a clinical epidemiological study, a multi-arm multi-site randomized controlled trial (RCT) [23] exploring the benefit of an integrated care pathway (ICP) for Long Covid, and mixed methods studies exploring inequalities of care and transferability of the ICP to other long-term conditions (LTCs) [24, 25]. This protocol forms the part of the STIMULATE-ICP study which aims to examine the inequalities in accessing Long Covid care.

Up to September 2022, three CAB meetings have taken place. The first meeting centred around refining the aims of the CAB and active case finding, while in the second the methodology of the active case finding was discussed. The discussions in both meetings have fed directly into this protocol. The third meeting’s purpose was to feedback on this protocol. Discussions in the first meeting were open to capture different ideas and perspectives from the CAB members. Following meetings have become more structured as the focus of this pilot study became clearer. Notes were taken at each CAB meeting and used to aid in the development of the agenda for the following meeting. Associated study materials have been shared with CAB members. Amendments and additions to these documents have been made based on their comments.

### Active case finding

‘Active case finding’ can refer to the use of a range of different mechanisms in community populations to identify individuals with specific health conditions that have previously not been clinically diagnosed [30]. Active case finding methodologies have previously been used to identify other illnesses including tuberculosis [30], leprosy [31] and Human Immunodeficiency Virus (HIV) [32] within communities using various community-based methods. The purpose of using an active case finding approach within this current study is to identify probable cases of Long Covid (as there is still no definitive laboratory test) in the population of defined geographical areas that have not already been clinically diagnosed.

#### Location and timing of the pilot

The London Borough of Camden has some of the highest levels of inequality in England [33]. Camden is a diverse borough–around 34% of people who reside there are from an ethnic minority background. There are also some areas within Camden with high levels of deprivation, with some areas falling with the 10–20% most deprived in the UK using IMD [34].

The research team have developed links with Camden voluntary organisations who have experience of, and are highly skilled at, identifying people in need in the community. This includes Voluntary Action Camden (VAC), who co-ordinate and deliver Community Links, for the social prescribing service in the borough and have in-depth knowledge of the locality. The aim of social prescribing is to improve mental and physical health outcomes by signposting and referring individuals to services that can make differences to health. Social prescribing recognises that physical and mental health outcomes can be influenced by ‘social, economic, and environmental factors’ and aims to provide support for individuals that take these different elements into consideration [35]. Furthermore, some evidence suggests that these improvements in health outcomes can be made through social prescribing [36]. Residents in Camden can self-refer for the local social prescribing service, but referrals also come from health services [37]. VAC have recently began receiving referrals from the University College Hospital (UCLH) post-covid clinic as part of a pilot pathway to see if social prescribing can have a positive impact on patients living with Long Covid. The research team and voluntary organisations will collaborate to identify probable cases of Long Covid in the community. In this site, this study is expected to be completed within 9 months from its start.

#### Recruitment

An easy read leaflet has been co-developed with the CAB to raise awareness of Long Covid symptoms and functional impact in the communities being targeted for recruitment (Fig 1). It describes the criteria for inclusion and the aim of the project. It will also form the basis of an easy read advert on community newsletters and digital outlets.

**Fig 1 pone.0284297.g001:**
[figure not shown]
Study recruitment easy read leaflet.

The recruitment material will be further tailored to be used as educational and awareness-raising materials and to suit the target population based on the findings from this pilot study. We will seek feedback on the material as one of the study outcomes. All educational materials developed based on the findings will be reviewed by the CAB and input incorporated before finalising.

VAC’s social prescribing team will aid the research team with recruitment by distributing materials during their usual activities and in contacts with individuals referred to their service. The research team will be working with a range of community organisations who work with different population groups to disseminate study information. These include food aid charities, organisations which work with ethnic minorities and organisations who work with people with disabilities, including learning disabilities. Recruitment will also be targeted towards support groups (online and offline), social media, community venues, faith groups, colleges/universities, leaflets in pharmacies, adverts in local press or community newsletters, housing associations, food banks, resident groups in accommodation/estates.

#### Eligibility criteria

The target population is any adult aged 18+ based in Camden without a clinical diagnosis of Long Covid who meets the criteria below, with a focused attempt to include people from ethnic minority backgrounds, individuals living in areas of Camden that are in the top 20% most deprived areas in England (IMD [6]), individuals with disabilities, including learning disabilities, and people who are employed in frontline roles within education and health and social care. A clinical diagnosis in this context means receiving a diagnosis in primary care.

For the purposes of this pilot study, a ‘probable’ Long Covid case, is an individual who has had a confirmed or suspected SARS-CoV-2 infection and fit the inclusion criteria below (Fig 2) but has not received a formal clinical diagnosis.

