**Fig 2 pone.0284297.g002:**
[figure not shown]
Probable Long Covid definition for study inclusion.

*Stage 1 (reaching out)*. The study’s promotional material will use the criteria from the WHO Clinical Case Definition of Post COVID-19 condition to raise awareness for consideration of potential participants who may be experiencing Long Covid [3]. These include:

History of probable or confirmed (by rapid antigen or PCR testing) SARS-CoV-2 infection three months or more from the time of recruitmentProlonged symptoms after infection (a list of the 10 most common symptoms will be provided) lasting at least 2 months that cannot be explained by an alternative or previous diagnosisSymptoms have an impact on everyday functioning

Potential participants who think they fulfil the above criteria will be encouraged to contact the research team by phone or email. A member of the research team will go through a set of questions for stage 2 screening below.

The 10 most common symptoms highlighted: Exhaustion/fatigue, cognitive dysfunction (brain fog, memory problems, concentration problems, occasional confusion), breathlessness, headache, muscle aches, palpitations, chest tightness/pressure/pain, dizziness, sleep disturbance and joint pain.

*Stage 2 (screening criteria)*. A screening questionnaire will be administered by a member of the research team to check eligibility. The above three criteria will be checked first. To be specific, the potential participant will be asked whether they had confirmed or probable COVID-19 at least 3 months ago, whether than have experienced prolonged symptoms not explained by a pre-existing health condition for at least 2 months after infection, and whether these symptoms restrict or limit their daily activities.

If the answer is yes to all three, a question will be asked whether the potential participant has an existing clinical diagnosis of Long Covid. If the answer is no, further questions about specific symptoms and their pattern will be asked. Given the evidence that Long Covid is predominantly a multi-system condition [7], participants will be included if they have three or more of the symptoms listed below. The choice of three symptoms as a cut-off was made based on the evidence which points out that Long Covid is predominantly a multi-symptom and multisystem condition [7, 38, 39], and discussions with CAB.

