Post-exertional symptom exacerbation (symptoms such as fatigue, difficulty thinking, pain recurring after remission or getting worse following exertion, either immediately or up to 72 hours post exertion) [40], exhaustion, cognitive dysfunction (brain fog, memory problems, concentration problems, occasional confusion), breathlessness, headache, muscle aches, palpitations, chest tightness/pressure, chest pain, dizziness, sleep disturbance, joint pain, leg pain, pins and needles feeling, tinnitus, sore throat, cough, nasal symptoms, hoarse voice, abdominal pain, nausea, diarrhoea, chills, altered or loss of sense of smell, altered or loss of sense of taste, skin rash, loss of appetite and sneezing.

The above screening process form the criteria for inclusion in the study rather than a tool upon which clinical decisions are made. Those who fulfil the stage 2 screening criteria will be assumed to have probable Long Covid and asked if they are interested to take part in the study.

Participants will be asked to read the Participant Information Sheet (PIS) in paper or digital format. A member of the research team can also read it to them, or they can watch a short video describing the study using the same information included in the PIS. If they are interested to take part, they will be asked to complete the study’s consent form (in paper or online version). Arabic, Somali and Bengali are three of the most spoken community languages in Camden [41]. If needed, Arabic, Somali, and Bengali versions of the PIS short video can be provided. Study documents can be translated into these community languages if this is required following an assessment of recruitment progress 6 weeks into the study. Some participants, especially those with additional needs or those who speak community languages, may prefer to have the documents read and/or explained to them by a friend, carer, or voluntary organisation worker. Whether they opt in the study or not, they will be directed to NHS resources and/or NHS 111 website for further information about the kind of help they can seek regarding their symptoms. Fig 3 shows the eligibility screening and participant flow chart.

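### Eligibility tests only for a clinical diagnosis, glossed as a primary-care one, while the stated target also requires no referral to, or use of, Long Covid services

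*Protocol article*

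**What the plan says.** **Target.** The Abstract sets out to test a community approach to "identifying Long Covid cases that have not been clinically diagnosed and have not been referred to Long Covid specialist services". The last paragraph of the Background pairs absence of a diagnosis with absence of care. The second objective is a sampling frame of people who do not access NHS Long Covid services. One listed outcome is a description of those found who are not accessing care, and the Discussion describes the cases in similar terms.

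**Eligibility rule.** Under Eligibility criteria, the population is adults based in Camden without a clinical diagnosis, and "A clinical diagnosis in this context means receiving a diagnosis in primary care". In Stage 2, three questions cover infection at least 3 months ago, symptoms lasting at least 2 months, and limitation of daily activities. Then "a question will be asked whether the potential participant has an existing clinical diagnosis of Long Covid". Those who answer no go on to the symptom list and need three or more. The text adds that "The above screening process form the criteria for inclusion in the study", and that "Those who fulfil the stage 2 screening criteria will be assumed to have probable Long Covid".

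**Recruitment route.** Under Location and timing of the pilot (and again under Community care pathway), "VAC have recently began receiving referrals from the University College Hospital (UCLH) post-covid clinic". Under Recruitment, the same organisation's social prescribing team helps by "distributing materials during their usual activities and in contacts with individuals referred to their service".

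**The concern.** The study asks why people with probable Long Covid have not reached recognition and care. Non-access is part of what defines the people it wants to hear from, yet the written rule does not test it.

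At stake is the sampling frame. Someone already seen by a specialist service is likely to describe different barriers, and perhaps different experiences of stigma, from someone no service has recognised. The expected size is 20–30 interviews, so a few such participants could colour the themes. The outcome describing people not accessing care would then cover some who are. No calculation in the protocol is affected.

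**Working it through.** No arithmetic applies. The expected number of interviews rests on data saturation, and the document gives no rate or power calculation. The check is whether the written rule selects the stated target.

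**Step 1: the two conditions.** The Abstract's target is *no clinical diagnosis* AND *not referred to specialist services*. Objective 2 uses *not accessing services*. The written rule is *no clinical diagnosis* alone, with diagnosis defined by a primary-care gloss. The second condition is absent from the described sequence.

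**Step 2: run cases through the rule.** Assume each person meets the three opening criteria and has three or more listed symptoms. The diagnosis item can be read in two ways: the question as worded in Stage 2 (any existing clinical diagnosis), or with the primary-care gloss applied.

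| Person | Question as worded | With primary-care gloss | In the target? |
|---|---|---|---|
| A. Diagnosed by GP | Excluded | Excluded | No |
| B. Diagnosed at the post-Covid clinic, no primary-care diagnosis | Excluded | **Admitted** | No |
| C. Seen at the clinic, reports no diagnosis | **Admitted** | **Admitted** | No |
| D. Referred, not yet seen, no diagnosis | Admitted | Admitted | No by the Abstract; yes by Objective 2 |
| E. No diagnosis, no referral | Admitted | Admitted | Yes |

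Rows B and C are the leak. B depends on how the interviewer applies the gloss; C gets through on either reading. Row D shows that the document's own statements of the target disagree.

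**Step 3: can such people reach screening?** Yes, by two documented paths.

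- The clinic refers patients to the partner organisation, and that organisation gives study material to people referred to it. This can produce B or C.
- Under Community care pathway, social prescribers can refer people to the clinic, and participants signposted by the partner may speak to a social prescriber before they contact the research team. This can produce D through the pilot's own pathway.

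**Step 4: is it caught later?** The interview prompts cover the forms of care and support sought, so B, C and D might be recognised then. That is after consent, and the protocol states no rule for handling them.

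**The case against.** Several points on the other side have force.

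- *The Stage 2 question is not limited to primary care.* The definition of a probable case also refers to a formal clinical diagnosis without restriction. Many clinic patients would answer yes and be excluded, and those referred by their GP may hold a GP diagnosis as well. This stands. It narrows the leak without closing it: row C remains, and the gloss leaves row B open.
- *The leaflet, the inclusion-definition figure, the flow chart and the questionnaire are not visible here.* One of them may hold a service-contact item. That is possible. However, the running text gives the sequence step by step and says it forms the inclusion criteria, so the text needs correcting in either case.
- *Not referred and not accessing are different conditions.* This is right. Excluding everyone ever referred would remove people referred but never seen, who fit Objective 2 and bear directly on access barriers. The fix must respect this.

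Three stronger readings are tempting, and the document does not support them. A reader might infer that this route contradicts the statement under Ethics and risk management that participants come from the community. It does not: the partner is a voluntary organisation, and recruiting through it is community recruitment even where the NHS referred some clients. A reader might also infer that a sizeable share of interviews would be affected. The document does not give the clinic-referred share of the partner's clients, the partner is one of many channels, and the clinic pathway is a recent pilot. Finally, a reader might infer that a case-finding yield would be inflated, but the listed outcomes are descriptive and developmental and include no case count or yield threshold.

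**Conclusion.** The mismatch is real. The target is stated with a non-referral or non-access condition in several places, and the eligibility text omits it while narrowing the diagnosis condition to primary care. Following the written rule, a person under the post-Covid clinic who has no primary-care diagnosis, or reports none, can be enrolled as an unrecognised case, and a documented recruitment route leads to such people.

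The size cannot be stated. It depends on the partner's client mix, on the share of enquirers who come through that channel, and on how the diagnosis question is asked and answered. The consequence is for the interpretation of the interviews and of the outcome on people not accessing care. The conclusion assumes that the running text reflects the screening questionnaire in use; if the questionnaire already asks about service contact, the remaining task is to make the text agree with it.

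**What to change.** 1. Under Eligibility criteria, define clinical diagnosis as a Long Covid or post-Covid diagnosis by any clinician in any setting, and use that definition in the Stage 2 question.
2. Add one Stage 2 question: whether the person has been referred to, or seen by, a Long Covid or post-Covid service.
3. Treat people already seen by such a service as outside the target.
4. Record people referred but not yet seen, including those referred by the social prescribing partner, and report them separately.
5. Reconcile the Abstract (not referred) with Objective 2 (not accessing), and align the Background, Outcomes and Discussion with the result.

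The cost is a revised definition, one added question in a questionnaire that the team already administers, and a minor ethics amendment. A few enquirers who would now be enrolled will be screened out.
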